### Sample size calculation

3.5

The sample size calculation formula is as follows: 

[figure not shown]

In the above formula, *N* is the number of samples in each group, *p*_0_ is the incidence of outcomes in the non-exposed group, *p*_1_ is the incidence of outcomes in the exposed group, *c* is the ratio of the number of non-exposed and exposed groups, *α* is an acceptable type I error, *β* is an acceptable type II error, and *Z*_α_ and Z_*β*_ can be determined by looking them up in the *Z* value table.

The 1-year survival rate is expected to be 22% in the non-exposed group and 45% in the exposed group. Assuming a non-exposed group and an exposed group sample ratio of 1:1, the required sample size is estimated by SAS 9.4 software ([name]) to be at least 134 cases in the 2 groups, based on a 2-sided alpha at a significance level of 0.05 and the test efficacy 1-beta of 80%. Meanwhile, considering a dropout rate of 15%, we concluded that a total of 148 patients would need to be recruited to ensure significant results.

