### Determination of grouping

3.7

Patients will be divided into a non-exposed group (Western medicine treatment group) and an exposed group (integrated traditional Chinese and Western medicine treatment group), according to whether they will receive TCM treatment or not. The classification of the cohort is based on the time of exposure after all clinical data are collected, not set at the time of enrollment.

1.Western medicine treatment group: times of chemotherapy ≥2 courses.2.Integrated traditional Chinese and Western medicine treatment group: TCM treatment ≥12 weeks, times of chemotherapy ≥2 courses, TCM and Western medicine treatment can be performed simultaneously or before and after.

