#### Data analysis

4.3.4

All statistical analyses will be performed using Statistical Packages of Social Sciences software (SPSS). A one-sided test (validity) will be used for all major efficacy indicators, and *P* values ≤.05 will be considered statistically significant. The measurement data will be expressed as the mean ± standard deviation, and the count data will be expressed using frequency and percentage. For quantitative indicators such as age, it is necessary to check whether the data meet the precondition of normality and homogeneity of variance. If the above conditions are met, a *t* test of measurement data of group design will be adopted. If only normality and not homogeneity of variance are satisfied, the calibration *t* test of measurement data in group design will be adopted. Otherwise, the Wilcoxon rank sum test will be used. For qualitative indicators such as sex, the general chi-square test will be performed according to the statistical analysis method corresponding to the data of the contingency table. If there is a frequency with a theoretical frequency <5, Fisher exact test will be used to directly calculate the exact probability. For survival data, the survival limit will be used to calculate the survival times of 25%, 50%, and 75% of each cohort. The log-rank test will be used to compare the survival rate, and the corresponding survival curve will be obtained.

For the analysis of influencing factors of efficacy, the univariate Cox regression model will be adopted in the first screen (*P* < .10), and the screened variables will then be fitted to the multivariate Cox regression model (*P* < .05).

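### The only multivariable survival model chooses its covariates by P value, so it can lose weak-to-moderate or masked confounders and does not guarantee that TCM exposure stays in.

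*Protocol article*

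**What the plan says.** Determination of grouping in the protocol article forms the two cohorts "according to whether they will receive TCM treatment or not", so there is no randomisation.

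The Data analysis section then gives two survival analyses:

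- **Group comparison.** "The log-rank test will be used to compare the survival rate". No stratification or adjustment is described.
- **Multivariable model.** This is introduced with "For the analysis of influencing factors of efficacy". In it, "the univariate Cox regression model will be adopted in the first screen" at P < .10, and "the screened variables will then be fitted to the multivariate Cox regression model", with P < .05 given in brackets.

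No covariate is named as kept whatever its P value, and TCM exposure is not said to be forced in. The same section sets the sidedness: "A one-sided test (validity) will be used for all major efficacy indicators".

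**The concern.** In a cohort grouped by treatment received, a baseline variable needs adjustment when it is related to both exposure and survival. Its univariate P value with survival does not settle that. A prognostic factor of moderate strength often misses P < .10 in a study of this size. One that is more common in the group with the better treatment effect can have its own effect masked, and so fails the screen precisely because it confounds.

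The protocol describes no other adjusted survival analysis. If an adjusted TCM effect is reported, this rule decides what it is adjusted for, and whether TCM is in the model at all. The size of the estimate and the error rate of its test are at stake. The direction of bias is not known in advance, because it depends on which group has the worse prognosis.

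**Working it through.** **Plan figures used.** Sample size calculation states: "The 1-year survival rate is expected to be 22% in the non-exposed group and 45% in the exposed group", and "Assuming a non-exposed group and an exposed group sample ratio of 1:1". With two-sided alpha 0.05, 80% power, pooled variance and no continuity correction:

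n per group = [1.960 × √(2 × 0.335 × 0.665) + 0.842 × √(0.22 × 0.78 + 0.45 × 0.55)]² / 0.23² = 64.9, so 65 per group and 130 in total. This is within 3% of the plan's 134, so the survival inputs are read correctly. The plan gives no figure for the Cox rule itself.

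**Expected deaths (assumption: exponential survival, uniform accrual, follow-up 16-31 months).** The implied HR is ln 0.45 / ln 0.22 = 0.527. Monthly hazards are 0.1262 and 0.0665. The expected proportions dying are about 94% and 78%, which gives about 127 deaths with 148 patients. If 15% are lost (126 patients), it is about 108-109. A round 120 lies inside that range.

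**Chance that a true factor fails the screen.** For a binary factor with prevalence q and D deaths, z = √(D·q·(1−q)) × |ln HR|. The pass probability is Φ(z − 1.645) at P < .10 and Φ(z − 1.960) at P < .05.

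- D = 120, q = 0.5, HR 1.4: z = √30 × 0.3365 = 1.84. It passes P < .10 in 58% (fails 42%) and P < .05 in 45%.
- D = 120, q = 0.5, HR 1.3: z = √30 × 0.2624 = 1.44. It passes P < .10 in 42% (fails 58%) and P < .05 in 30%.

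Failure at P < .10 as prevalence falls from 50% to 20%:

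| Factor HR | 127 deaths | 109 deaths |
|---|---|---|
| 1.3 | 57-68% | 61-71% |
| 1.5 | 26-43% | 32-48% |
| 1.75 | 7-19% | 10-25% |
| 2.0 | 1-7% | 2-11% |

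**Masking.** In a simulation with 148 patients, TCM HR 0.527 and a confounder of HR 1.5 present in 50% of exposed and 30% of non-exposed patients, the confounder fails the first screen in 57-60% of runs. In the runs where it is lost, the TCM HR averages 0.56, against 0.52 with adjustment in the same runs. Here the bias is towards no effect.

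**Null simulation (true TCM HR 1.00).** Assumed: 74 per group and three confounders of HR 1.4, each at 40% in one group and 60% in the other, with TCM kept in every model. Ranges cover repeated runs of 1,000 to 2,000 studies; one-sided error is at .05 in favour of TCM.

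| Model | TCM HR | One-sided error | Two-sided error | Confounders kept |
|---|---|---|---|---|
| Unadjusted | 0.82-0.83 | 28% | 20% | 0 of 3 |
| P < .10 screen only | 0.97 | 7.2-7.6% | 5.5-6.2% | 1.9 of 3 |
| Screen, then elimination at P < .05 | 0.93-0.94 | 12-13% | 8.4-10% | 1.3 of 3 |
| All three forced in | 1.00-1.01 | 4.8-5.7% | 4.8-5.2% | 3 of 3 |

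With the confounders at HR 2.0 instead, the P < .10 screen keeps 2.9 of 3 and gives HR 1.00 with 5.2% one-sided error. Adding elimination gives 6.2%.

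**Chance that TCM itself fails P < .10 (q = 0.5).** At the design HR of 0.527 and 127 deaths, z = √31.9 × 0.640 = 3.61 and failure is 2.5% (4.6% with 109 deaths). Also with 127 deaths, failure is 11% at HR 0.60, 36% at HR 0.70 and 65% at HR 0.80.

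**The case against.** The strongest reply is that this model is not the treatment comparison. It is introduced as a search for factors that influence efficacy, and the comparison of groups is the log-rank test. A reader might infer that the plan designates the screened model as its confounder-adjusted TCM estimate. The text does not say so. What remains is that no other adjusted survival analysis is described, so an adjusted TCM effect has no other source.

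Second, the larger error rates need P < .05 to be a retention rule. The protocol names no stepwise or backward procedure, and the bracketed P < .05 may be only the significance level. That objection stands: on that reading the excess is the smaller 7-8% one-sided.

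Third, the confounder strengths are assumed. This also stands, and strong factors usually survive the screen. A flat statement that real confounders are dropped would go too far.

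Fourth, a reader might infer that TCM is likely to be screened out. At the protocol's own effect size that is remote, and silence about forcing it in could be a matter left to a fuller document. The thresholds, however, are a stated rule that such a document would have to override.

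Finally, one might claim that confidence intervals after selection are too narrow. The protocol article promises no intervals for this model and no coverage was calculated, so that claim is not made here.

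**Conclusion.** The concern holds in a limited form. The protocol fixes a P-value rule for its only multivariable survival model in a non-randomised cohort. Followed as written, the rule can lose weak-to-moderate or masked confounders, and possibly TCM.

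- **Loss of confounders:** about 42-58% at the first screen for a balanced factor of HR 1.3-1.4 with 120 deaths, but only a few per cent for a common factor of HR 2.0.
- **Effect on the TCM test:** in the assumed null scenario, modest under the first screen alone (HR about 0.97, 7-8% one-sided error) and clear if P < .05 also removes variables (about 0.94, 12-13%). Forcing the confounders in gives 5-6%.
- **Loss of TCM:** 2.5-5% at the design effect, about 36% at HR 0.70.

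The confounder hazard ratios, prevalences and event counts are assumptions, because the protocol gives none of them. This should be changed, but the size of the harm does not make it a fatal flaw.

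**What to change.** For the survival comparison of TCM with no TCM, specify one Cox model containing TCM exposure and a short list of baseline prognostic variables fixed in advance, all kept regardless of P value. Candidates that the article already mentions are stage, ECOG score, log CA19-9, age and sex. The data collection schedule should be checked to confirm that each is recorded at baseline.

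The expected deaths support this. With 7-9 parameters and about 108-127 deaths, events per parameter run from 108 / 9 = 12.0 to 127 / 7 = 18.1. Several categories for stage or ECOG use more parameters and should be counted.

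If the P-value screen is still wanted, keep it only as a labelled exploratory analysis of prognostic factors, with TCM retained in the model. State whether P < .05 there is a retention rule or a significance level.

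The cost is a change of wording and a few degrees of freedom. The change deals with measured baseline confounders only; it does not remove unmeasured confounding.

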#### Patient and public involvement

4.3.5

Patients and the general public were not involved in the design of the present study. Patients will be involved in the data collection process by providing information during data collection.

#### Ethics and dissemination

4.3.6

This work was supported by Beijing Municipal Science and Technology Commission and approved by the ethics committee of Guang’anmen Hospital, China Academy of Chinese Medical Sciences (Approval No. 2019-016-KY). All patients will sign a written informed consent prior to data collection. The results will be disseminated through peer-reviewed journals and conference presentations and will be openly shared after completion of the trial.

## Discussion

5

TCM has been used in China for thousands of years. In recent years, it has been gradually accepted by Western countries.^[19]^ In the literature,^[20,21]^ it has been reported that TCM plays an important role in reducing the side effects of chemotherapy and improving the survival of patients. In addition, studies^[22]^ have reported that TCM combined with chemotherapy can improve survival rates and quality of life. This study aims to assess the survival and quality of life of patients with advanced pancreatic cancer, refine the core pathogenesis of TCM for pancreatic cancer and core prescriptions, and ultimately provide reliable data support for the formation and application of clinical solutions for the treatment of pancreatic cancer using integrated Chinese and Western medicine.

### Strengths

5.1

This study has several advantages. First, this is a multicenter prospective observational cohort study involving 12 medical units in 9 provinces and cities in China, all of which are grade-3A hospitals. The results are reliable and can provide relatively objective evidence. Second, observational studies are more humane than randomized controlled trials (RCT). Moreover, it will lay a foundation for the standardization of integrated Chinese and Western medicine treatment to improve the curative effect, reduce the medical expenses of pancreatic cancer and the abuse and reuse of drugs, and generate certain social benefits for more patients with pancreatic cancer. This study involving 12 medical units in 9 provinces and cities in China, all of which are grade-3A hospitals, will generate relatively reliable results.

### Limitations

5.2

This study also has some limitations. The present study is a prospective cohort study with a small patient sample size. However, because of the lower incidence of pancreatic cancer relative to other cancers, the number of patients with advanced pancreatic cancer meeting the inclusion and exclusion criteria may be relatively small, which will result in a small sample size. Given the small sample size, the amount of data that can be collected from the integrated Chinese and Western medicine group may lead to results that are not as robust as would be feasible with a larger sample size. Because of the short study duration and funding constraints, only 148 advanced pancreatic cancer patients were eventually recruited. However, even after the end of the study, we will continue to follow the survival of subjects so as to more accurately analyze and evaluate the clinical efficacy of integrated Chinese and Western medicine in the treatment of pancreatic cancer.
